## Abstract

**Background:**

The use of e-cigarettes, or vaping, has increased exponentially in the past decade, particularly among youth. Emerging evidence indicates growing nicotine dependence among youth, revealing historically higher rates of dependence among current e-cigarette users compared to rates seen in earlier research. Despite the urgent need for youth vaping cessation interventions, there is limited knowledge about the process of vaping cessation, and few evidence-based interventions are available to young people seeking support. A notable literature review on vaping cessation resources for young people recommended technology-based interventions, such as smartphone apps and SMS text messaging services, as a promising area of vaping cessation research and intervention development.

**Objective:**

The primary aim of our study is to determine the effectiveness of the *Crush the Crave* app in supporting vaping cessation among youth recruited to the intervention arm via comparison with an assessment-only control group. The primary hypothesis is that participants in the intervention group—those using *Crush the Crave*—will be more likely to be abstinent at the 6-month follow-up point than participants in the assessment-only control arm.

**Methods:**

A 2-arm, single-blind, parallel randomized controlled trial will be conducted over 12 months. Study invitations will be sent to 600 youth (age: 16-18 years) and young adult (age: 19-29 years) e-cigarette users and randomized between an intervention arm, which will be using *Crush the Crave* (n=300), and an assessment-only control arm (n=300) in a 1:1 ratio. The primary hypothesis is that participants in the intervention group—those using *Crush the Crave*—will be more likely to be abstinent at the 6-month follow-up point.

**Results:**

Study recruitment began on March 4, 2022. Recruitment is anticipated to be completed in December 2022.

**Conclusions:**

This protocol describes one of the first-ever randomized controlled trial studies to evaluate the effectiveness of an app-based intervention for supporting vaping cessation among youth aged 16 to 18 years and young adults aged 19 to 29 years. The findings from our trial will help increase our understanding of the process of vaping cessation among youth and provide evidence on the effectiveness of an app-based intervention in helping young people quit vaping. The trial results will also have implications in the development of current and future approaches to youth vaping cessation.

**Trial Registration:**

OSF Registries osf.io/hmd87; https://doi.org/10.17605/OSF.IO/HMD87

**International Registered Report Identifier (IRRID):**

DERR1-10.2196/42956

## Introduction

The use of e-cigarettes, or vaping, has increased exponentially in the past decade, particularly among young people [1,2]. Emerging evidence indicates growing nicotine dependence among youth, revealing historically higher rates of dependence among current e-cigarette users compared to rates seen in earlier research [3-5]. Several studies have documented the growing need for vaping cessation support among youth [4-10]. In 2019, young people who did not smoke accounted for a greater number of regular vapers (as opposed to *ever-vapers*) when compared to those who smoked [11]. The COVID-19 pandemic may have exacerbated these conditions, with research suggesting an increase in substance use, including vaping, among young people [9,12,13].

Despite the urgent need for youth vaping cessation interventions, there is limited knowledge about the process of vaping cessation, and few evidence-based interventions are available to young people seeking support [6,14]. To date, much of the clinical and public health guidance on vaping cessation is adapted from the literature on smoking cessation [6,8,14]. However, while there are several commonalities between smoking and vaping, there are important differences that have received relatively little attention. A narrative review published in 2021 identified the following three key differences between vaping and smoking dependence: (1) greater variability in vaping products than in cigarettes, (2) the discreetness and convenience of vaping, and (3) greater social acceptability of vaping among youth [6,8,14]. Knowledge of these differences can inform the development of vaping cessation interventions that are effective and acceptable among young people.

Previous work in intervention research and development identified technology-based interventions as a promising area for promoting youth vaping cessation [6]. Smartphone technology and mobile software apps are highly accessible, easily scalable, and cost-effective platforms for mental health interventions [15]. Globally, young people born after the year 2000 are the top smartphone users [16,17]. Consequentially, vaping prevalence is also greatest among those aged 18 to 24 years and 15 to 17 years [11,18,19]. In fact, the use of apps for addressing mental health and substance use among youth is well documented in the literature [20-23], with apps for vaping cessation being among the latest additions [24]. However, there is currently no empirically tested smartphone app that specifically targets youth vaping cessation [24].

This protocol describes one of the first-ever randomized controlled trial (RCT) studies to evaluate the effectiveness of an app-based intervention for supporting vaping cessation among youth. The first-ever RCT of a vaping cessation intervention was designed to evaluate the effectiveness of an SMS text messaging program called *This is Quitting* in helping young adults in the United States aged 18 to 24 years to stop vaping [8]. The trial results showed that an SMS text messaging program that provided interactive and tailored messages was successful in promoting vaping cessation among young adults [8]. However, this trial did not include youth aged 14 to 17 years, for whom vaping cessation is urgently needed, as participants [1,4,18]. In our study, 600 youths (aged 16-18 years) and young adults (aged 19-29 years) who vape will be recruited. The intervention is called *Crush the Crave*—a comprehensive, full-featured app for supporting youth vaping cessation (Figure 1).

*Crush the Crave* for vaping cessation was developed based on an earlier version of the app for smoking cessation [25-27]. An RCT of 1599 young adult smokers assessed *Crush the Crave* for smoking cessation and found that the 30-day point prevalence abstinence (PPA) at 6 months for the intervention condition (118/820, 14.4%) was not significantly different (odds ratio 0.82, 95% CI 0.63-1.08) from that for the control condition (132/779, 16.9%). However, the rate of abstinence was favorable when compared with the unassisted 30-day quit rates of 11.5% of young adults [28]. In addition, it was determined that 61% of the young adult smokers in the RCT were vaping. The increasing nicotine dependence and use of vapes among youth have prompted interest in developing an app for vaping cessation based on people’s experiences with *Crush the Crave* for smoking cessation. *Crush the Crave* is a tracker app that tracks the following information: the number of vape-free days and the amount of money saved since quitting vaping, as well as triggers and cravings. The app also provides the following functions: tailored supportive messages and inspirational graphic images for quitting vaping, personalized quit plans, graphic performance feedback, digital awards for achieving milestones, the reporting of vaping triggers, assistance for dealing with cravings, and links to other supportive resources that can aid in vaping cessation.

The primary aim of our study is to determine the effectiveness of the *Crush the Crave* app in supporting vaping cessation among youth recruited to the intervention arm via comparison with an assessment-only control group. The primary hypothesis is that participants in the intervention group—those using *Crush the Crave*—will be more likely to be abstinent at the 6-month follow-up point than participants in the assessment-only control arm. Our trial is currently open for recruitment. The anticipated completion date for our study is March 2024.

**Figure 1 figure1:**
[figure not shown]
*Crush the Crave* app: comparison of the old version for young adult smoking cessation and the current version for youth vaping cessation.

## Methods

### Trial Design

A 2-arm, single-blind, parallel RCT will be conducted over 12 months. Study invitations will be sent to 600 youth and young adult e-cigarette users and randomized between an intervention arm, which will be using *Crush the Crave* (n=300), and an assessment-only control arm (n=300) in a 1:1 ratio. The trial protocol is registered with the Center for Open Science (registration digital object identifier: 10.17605/OSF.IO/HMD87). The trial protocol was developed in accordance with the SPIRIT (Standard Protocol Items: Recommendations for Interventional Trials) 2013 checklist of recommended items for interventional trials [29].

### Ethics Approval

The study is being conducted by the Ontario Tobacco Research Unit. Approval for the study protocol was obtained from the University of Toronto Office of Research Ethics (protocol number: 00038410).

### Recruitment and Enrollment

Eligible participants are youth aged 16 to 29 years who live in Canada and have used nicotine e-cigarettes in the previous 30 days. Study participants will be recruited through the Vaping Dependence Cohort—an existing panel of youth enrolled in a prospective cohort study at the University of Toronto who provided consent for recontact in future studies at the Ontario Tobacco Research Unit. This panel is comprised of a broad sample of youth who self-reported current or past regular use of nicotine e-cigarettes. The use of nicotine e-cigarettes was assessed through a question that asked respondents if they had used e-cigarettes daily, in the past week, in the past month, in the past 3 months, or in the past year and if they had ever used an e-cigarette. This cohort was designed to balance recruitment by smoking status (*ever* or *never*), e-cigarette use (*ever* or *never*), and age (16-18 years or 19-25 years). Consequently, the prevalence of smoking, e-cigarette use, and younger participants was higher than what would be expected in a simple random sample of the population. An analysis controlling for the study design elements found that the within-group characteristics of the included youth were broadly consistent with expectations, which were based on a representative sample [9].

### Informed Consent

After eligibility screening, participants must provide informed consent to proceed with study enrollment. The web-based consent form contains information about the study, the *Crush the Crave* app, participant eligibility, requirements and expectations for study participation, compensation, data collection, and plans for protecting participants and their privacy (ie, data deidentification), as well as the contact information of study staff and the University of Toronto Office of Research Ethics. Those who agree to participate in the study will receive an email containing a link to download the *Crush the Crave* app (sent to the email addresses they provided).

### Compensation

Each participant in the intervention and control arms will receive compensation (CAD $10 [US $7.46] electronic gift card) upon completion of the baseline survey questionnaire and each time they complete a follow-up survey throughout the course of the study.

### Randomization

Eligible participants will be identified from the Vaping Dependence Cohort. The *rand()* function in Excel (Microsoft Corporation) allowed for simple randomization; the top 50% highest numbers identified the participants that will receive invitations to use the *Crush the Crave* app. A research assistant from the Vaping Dependence Cohort will conduct the randomization and create a variable with a blinded key for the initial data analysis, which will allow the investigators and analyst to be blinded to the group allocation up until the data analysis is complete.

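### The eligible panel list is halved by one unstratified draw, although vaping frequency, smoking status and age group are already on file; stratifying would add a little precision (low priority)

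*Protocol article*

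**What the plan says.** All places are in the Methods of the protocol article.

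- **Randomization.** The list comes first: "Eligible participants will be identified from the Vaping Dependence Cohort". Each person gets an Excel random number, which "allowed for simple randomization; the top 50% highest numbers identified the participants that will receive invitations" to use the app. No stratum, block or minimization factor is named. A research assistant "will conduct the randomization and create a variable with a blinded key".
- **Trial Design.** "Study invitations will be sent to 600 youth and young adult e-cigarette users and randomized between an intervention arm" and a control arm, 300 each, 1:1.
- **Recruitment and Enrollment.** The panel asked whether members had "used e-cigarettes daily, in the past week, in the past month, in the past 3 months, or in the past year". "This cohort was designed to balance recruitment by smoking status", by e-cigarette use, "and age (16-18 years or 19-25 years"). Trial eligibility is age 16 to 29 with nicotine e-cigarette use in the previous 30 days.
- **Outcome Measures.** Success is 30 days without a puff.
- **Data Analysis Plan.** The number needed to treat comes from an adjusted risk difference. The only covariates listed are those of the imputation model. They include age and vaping dependence, but not vaping frequency or smoking status.

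**The concern.** The whole list is known before anyone is allocated, and three candidate stratifiers are already recorded for it. The panel was built around smoking status, e-cigarette use and age, yet the draw uses none of them.

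Vaping frequency is the one that matters most. Entry is open to anyone from a daily vaper to someone with a single use in the past month, and success is no use over a 30-day window. An occasional user therefore starts much nearer to success than a daily user. If one arm happens to receive more occasional users, its abstinence rate rises for reasons unrelated to the app. The planned difference is small, so precision is worth protecting where it is nearly free.

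**Working it through.** **Planned effect.** Sample-size inputs in the Data Analysis Plan: control rate 5%, odds ratio 1.60. Odds = 0.05/0.95 × 1.60 = 0.0842, so the app-arm rate is 0.0842/1.0842 = 7.77% and the planned difference is 2.77 points. (The stated 600 does not follow from these inputs: the usual two-proportion formula needs 1,225 responders per arm, two-sided, at 80% power. That is a separate and larger matter, and nothing below depends on it.)

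**Ordinary sampling error.** SE of the risk difference = √[(0.05×0.95 + 0.0777×0.9223)/n].
- n = 300 per arm: 2.0 points, 95% half-width 1.96 × 1.99 = 3.9 points.
- n = 225 per arm (the planned 75% response): 2.3 points.

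**Chance imbalance.** For a binary factor with prevalence p, the SD of the between-arm difference is √[p(1−p)×2/300]: 4.1 points at p = 0.5, 3.7 at 0.3, 3.3 at 0.2. The exact hypergeometric distribution for halving a list of 600 gives:
- a difference of 5 points or more: probability 0.18 (p = 0.3) to 0.22 (p = 0.5);
- a difference of 10 points or more: 0.01 to 0.02.

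**Effect on the estimate.** The documents give neither the share of occasional vapers nor the gap in quit rates, so both are assumed over a range. The 95% shift is 1.96 × SD × gap. The share of outcome variance is p(1−p)×gap² divided by the outcome variance.

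| Prevalence p | Gap in quit rate | 95% shift in risk difference | Share of variance |
|---|---|---|---|
| 50% | 3 points | 0.24 points | 0.4% |
| 50% | 5 points | 0.40 points | 1.0% |
| 50% | 8 points | 0.64 points | 2.7% |
| 50% | 6 points (8% vs 2%) | 0.48 points | 1.9% |
| 30% | 10 points (12% vs 2%) | 0.73 points | 4.4% |
| 20% | 15 points (17% vs 2%) | 0.96 points | 7.6% |

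The first three rows use the variance at the mean planned rate (6.39%). The last three use 0.05 × 0.95, because each averages to 5% overall (for example 0.3×12 + 0.7×2 = 5.0).

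**What stratifying buys.** Removing 0.4% to 7.6% of the variance multiplies the half-width by √(1 − share), that is 0.998 to 0.961. The 3.9 points shrink by about 0.01 to 0.15 points. Expressed as sample size, 600/(1 − share) gives about 602 to 649.

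**Events available for adjustment.** 225 × (0.05 + 0.0777) ≈ 29 among responders, or 300 × (0.05 + 0.0777) ≈ 38 among all randomized. Across eight cells that is about 4 to 5 events per cell.

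**The case against.** The strongest reply is that nothing here is an error. A random half-split of 600 people is valid, chance imbalance is already inside the standard error, and type I error and coverage hold. This stands. Even the largest shift in the table, 0.96 points, is under half of one SE.

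The analysis mentions an adjusted risk difference, and a baseline questionnaire collects vaping data in both arms, so covariate adjustment could recover most of the loss. This also stands in large part. With 29 to 38 events, however, there is limited room for adjustment, and no outcome-model covariates are named.

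Stratifying is not quite free either. The split decides who is invited, so consent and the planned 25% non-response erode the balance. Panel values may be out of date, and the panel's age bands stop at 25 while the trial runs to 29. These points reduce the gain without abolishing it.

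A reader might infer more than the documents support:
- *That the draw is unrestricted.* The article's word is simple, but taking the top half fixes equal arms. A true coin toss would leave the arms 30 or more apart with probability 0.24.
- *That the factors are strongly prognostic.* No section relates any of them to quitting. For vaping frequency the link is a reasoned inference from the entry and success definitions; for smoking status and age there is not even that. The chance that at least one of three independent factors differs by 5 points or more, 0.45 to 0.53, therefore says little about the estimate.
- *That the allocation cannot be reproduced because Excel random numbers recalculate.* The article does not say the values were left live, and it describes creating a coded group variable. How values were frozen is a detail that a condensed article may leave out.

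**Conclusion.** The point holds as a modest design improvement. The stated method ignores recorded information that could have balanced the arms on vaping frequency. The result is a slightly less precise estimate, not a biased one: about 0.4% to 8% of outcome variance, under assumed prevalences of 20% to 50% and assumed quit-rate gaps of 3 to 15 points. The upper end needs a 17% versus 2% contrast between occasional and daily vapers, which the documents neither support nor exclude. The calculation also treats balance among those randomized as carrying through to those analysed, so the realised gain would be smaller. Priority is low.

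**What to change.** The Randomization section mixes past and future tense, and the Results section says recruitment began on March 4, 2022, so it is unclear whether the draw has been made.

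**If it is still to be made:** halve the eligible list within strata, at least by vaping frequency (daily / less than daily) and, if cell sizes allow, by smoking status (ever / never) and age group (16-18 / 19 and over). All three give eight cells averaging 600/8 = 75 people. Use a seeded script and save its output before invitations go out. Carry the stratifiers into the primary model as main effects, not as eight separate cells, because events are few. Add vaping frequency and smoking status, where used, to the imputation model so that the two models agree.

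**If it has been made:** archive the allocation list as drawn. Before unblinding, prespecify adjustment for baseline vaping frequency, stating whether the panel value or the baseline questionnaire value is used.

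**Cost:** a short script, a sentence or two of text and slightly more analysis work, with no added participants or data. The balance gained applies to those randomized and is partly lost through non-acceptance and non-response.

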### Interventions

#### 
Crush the Crave

An earlier version of the *Crush the Crave* app was developed for smoking cessation [22,25], incorporating fundamentals of persuasive technology [30] and recommended practices for addressing tobacco use and dependence [31]. This evidence base formed the foundation for the current version of the *Crush the Crave* app for vaping cessation (Figure 2), which was redesigned (using principles of co-design [32]) by a multidisciplinary team of tobacco control researchers, design researchers, and software developers. Youth and young adults who vape were also engaged in the co-design process through a series of focus groups (January to February 2020) and an intensive design research workshop called *VapeHack* (May 2020).

Like the original app for young adult smoking cessation, *Crush the Crave* for vaping cessation enables users to customize a quit plan. As a tracker app, *Crush the Crave* monitors the amount of money saved and the number of vape-free days since the user’s quit date. This savings calculator is one of the most significant changes in this version of *Crush the Crave*, which involved the conversion of the money saved based on the number of cigarettes smoked in a day to the money saved based on the number vape pods used in a week (calculated as the number of vape-free days multiplied by the product of the average number of vape pods used each day and the price of vape pods in Canada). The previous version of the app had a health calculator that monitored users and informed them of the health milestones achieved since quitting smoking. In the current version of the app, the health calculator feature was removed as a reflection of the lack of definitive evidence on the health effects of vaping. Further development of *Crush the Crave* for vaping cessation will be halted during the trial.

The app also tracks cravings and vaping habits through a diary of vaping triggers that records when, where, and why vaping occurs. The app displays supportive messages and graphic images of encouragement in response to cravings and relapse, as well as direct links to evidence-based resources, such as quitlines. A visual representation of quitting progress over time is provided to users on the main page, and users have the ability to upload personalized pictures and verbal affirmations. *Crush the Crave* also gives users the ability to geotag where vaping and cravings occur, and this information is only viewable to the user. Other features include reminders or push notifications regarding the money saved, health improvements, and the achievement of goals; digital awards for reaching milestones; and supportive messages tailored to where users are in the quitting process.

**Figure 2 figure2:**
[figure not shown]
*Crush the Crave* app on the Google Play Store.

#### Assessment-Only Control

Based on an approach that is similar to the one used by Graham and colleagues [8], participants will be invited via email to complete the baseline assessment, and they will be invited to complete the follow-up assessment questionnaires asking about e-cigarette use and abstinence (as outlined in the following sections) at 3, 6, 9, and 12 months. At the end of the intervention period and following the last follow-up assessment, they will be invited to try the *Crush the Crave* app, if they are interested.

### Data Collection

A baseline questionnaire will be sent to both the intervention group and the control group, using a self-administered web-based survey. This will collect comprehensive data on the history and characteristics of vaping (eg, vaping dependence, use of e-cigarettes, and self-confidence to quit), self-perceived addiction to vaping, health status (including mental health, mood, and perceived stress), and current and previous history of the use of other substances (combustible cigarettes, marijuana, alcohol, hookahs, and other tobacco products). The baseline survey will also ask questions on environmental factors and cessation goals. Self-reported demographic data (age, sex, gender and sexual orientation, province and country of residence, race and ethnicity, education, and marital status) will also be collected in the baseline survey.

A follow-up survey will be sent to the control and intervention groups at 3, 6, 9, and 12 months. Responses to the follow-up survey will be used to analyze any significant changes in vaping habits and differences between groups. The follow-up survey questionnaire includes items on cross-contamination and the use of cessation methods.

